## Abstract

**Background:**

Hip fractures resulting from falls increase substantially with advancing age and less than half of older hip fracture survivors regain their former levels of mobility. There is increasing evidence that rehabilitation interventions with exercises that goes beyond the sub-acute phase or even in a later stage of care have a positive impact on various functional abilities. The purpose of this study is to determine if exercise program training for people who have suffered a fall-related hip fracture will improve functional mobility when compared with usual care.

**Methods:**

A randomized controlled trial with blinded assessors and intention-to-treat analysis will be undertaken. We will recruit 82 older adults, 60 years or over who have suffered a hip fracture due to a fall in the previous 6 to 24 months. Participants randomized to the Intervention Group (IG) will undertake a physical exercise program involving progressive and challenging balance training and neuromuscular and functional training of the lower limbs, conducted at home by physiotherapists, once a week, lasting about one hour, in the first, second and third month after randomization and will be taught to perform exercises at home, twice a week, using a booklet. Visits to monitor and progress the home exercise program will be conducted once a month, from the fourth to the sixth month and each 2 months until the end of the follow up at the 12^th^ month, i.e., a total of 18 sessions. Participants will receive monthly phone calls to encourage exercise adherence. The control group will receive usual care. The primary outcome will be mobility-related disability and participants will be assessed at baseline, and at 3 months, 6 and 12 months. Participants will receive monthly phone calls to ask about falls and exercise adherence. Adverse effects will be monitored.

**Discussion:**

This study proposes a home-based exercise program, which may in part overcome some barriers for rehabilitation, such as difficulties with public transportation and lack of a caregiver to accompany older patients to sessions. If a positive effect is observed this program has the potential to be incorporated into the public health system and contribute to building a pathway of care for older people with hip fracture.

**Trial registration:**

Clinicaltrials.gov Identifier: NCT02295527.

## Background

Over a lifetime, about half of women and a quarter of men will suffer a fragility bone fracture [1, 2], mostly due to falling [2]. Among the most serious and common fractures are hip fractures, which have significant risks of mortality [2] and disability [3]. It is estimated that in 2050 the global number of hip fractures will be between 7.3 and 21.3 million [4] and the cost with the treatment will be approximately of 131.5 billion US dollars [5].

Physical and psychological post-fracture limitations, such as decreased mobility [6] and lower limb strength [7], impaired balance [6], lack of confidence [7], fear of falling [6] and increased risk of falls [8] restrain about 40% of older people from returning to daily activities required to live independently and safely [3, 9].

Two years after injury more than half of older hip fracture survivors do not regain pre-injury functional abilities [10] and experience a moderate to high risk of further falls [6]. The restoration of mobility is crucial to enable old people to move around in and outside home, the recommended levels of physical activity, maintain social engagement and preserve autonomy. Ultimately, adequate mobility is a key component for an active and healthy ageing [11].

Although there is no consensus about the best intervention for improving functionality of older people after hip fracture [8], exercise programs delivered in an intensive and supervised basis, have been found to improve the mobility of these patients [8, 12, 13]. However, few studies have explored the late period of recovery (over 6 months) [14, 15], when functional limitations can persist due to inadequate dose as well as the type of exercise performed. Recently a home-based exercise intervention with minimal contact from a physiotherapist (4 visits) boosted by monthly telephone calls and the provision of a DVD version resulted in clinical meaningful improvement in the physical function of the lower limbs, but not in self-reported mobility and daily activities [16].

Over the next decades a huge increase in the older population will be experienced by low-and middle-income countries (LMICs), such as Brazil where population is ageing at one of the fastest rates in the world. The number of seniors in Brazil is predicted to double between 2002 and 2020, from 15 million to 32 million and to reach 64 million (30% of the total population) by 2050 [17]. Furthermore, people aged 80 and over will increase exponentially the next four decades, a growing and disproportionate demand on the health system and social support [17]. Along with an increased aged population LMICs will have to overcome barriers of care, such as difficulties in access and failure of existing health services to address older peoples’ rehabilitation needs. Yet post-fracture rehabilitation strategies are yet to be tested in low-and middle-income countries.

The primary aim of this study is evaluate the effectiveness of a physical exercise program for improving functional mobility in older people who have suffered a hip fracture due to a fall in the previous 6 to 48 months. Secondary aims to 1) determine the effects of the program in improving physiological risk for falls, functional and performance disability and quality of life; 2) establish predictors of adherence to the program and outcomes related to functional and mobility disability in older people after fall-related hip fracture.

## Methods

### Trial design

This is a randomized controlled trial with 12 months follow-up. The Ethics Committee on Human Research of the City University of São Paulo (CAAE: 27398814.7.0000.0064) approved the project. This study has been registered with the number protocol of NTC02295527 trials register.

After the baseline assessment an independent investigator, not involved with recruitment or data collection, will randomly allocate the eligible participants to one of two parallel groups by opening a sealed envelope with study group assignments i.e., a concealed allocation system. The randomization schedule will be prepared in advance by an independent investigator, not involved with recruitment or data collection, using in randomly-ordered blocks of 2, 4, and 6 participants. All assessors will be blinded to the group allocation, however, due to the trial design, participants and therapist are not able to be blinded to group allocation.

### Participants

Community-dwelling people aged 60 years and over, men and women, after a first hip fracture due to falling or bone fragility that has been surgically treated will be recruited. These participants will be in the later stage of rehabilitation phase (6 months to 2 years after the fracture). Participants will be recruited from public and private hospitals in São Paulo municipality, from rehabilitation services and through general advertisement.

Participants will be excluded if they have a severe cognitive impairment (assessed using the Mini Mental State Examination, with scores adjusted according to educational level [18] illiterate ≤ 13 points, 1 to 8 years of schooling ≤18 points and, 9 or more years of schooling ≤26 points); inability to walk despite using a walking aid; progressive or severe neurological disease (e.g., Parkinson’s disease, stroke) with severe functional limitations; communication disability that would impede intervention participation (severe uncompensated visual or hearing deficits); medical condition contraindicating exercise (e.g. unstable angina, severe heart disease, large or expanding aortic aneurysm, etc.); acute vertigo or dizziness less than 3 months duration; engaged in a regular exercise program with a frequency of at least twice a week 30min a day (excluding walking and senior dance).

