### Sample size calculation

The sample size of this study (41 participants per group) is sufficient to detect a change of 1.0 ± 1.48 points in the score of the Short Physical Performance Battery SPPB [32] with a statistical power of 80% and a significance level of 5%, considering a possible sample loss of up to 15%.

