### Statistical analysis

The comparison between groups on tests involving continuous variables (lower limbs functionality, physiological risk of falls, functional performance, quality of life and physical activity level) will be performed using linear models (General Linear Models-ANCOVA) adjusted for baseline values. The rate of falls will be compared between groups using negative binomial regression. Logistic regression models will be used to compare dichotomous variables between groups. All analyses will use the principle of intention-to- treat, in that participants will be analyzed according to their randomized assignment, regardless of whether they complied with the study protocol.

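### Time since fracture is known for everyone and varies widely, but neither the randomisation nor the ANCOVA names it; the possible cost is some precision, not bias

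*Protocol article*

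**What the plan says.** All references are to the protocol article.

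- **Entry window.** Participants: "These participants will be in the later stage of rehabilitation phase (6 months to 2 years after the fracture". The Methods part of the abstract agrees: "hip fracture due to a fall in the previous 6 to 24 months". The primary aim, at the end of the Background, has a different upper limit: "hip fracture due to a fall in the previous 6 to 48 months".
- **Randomisation.** Trial design describes concealed allocation from a schedule prepared in advance, "using in randomly-ordered blocks of 2, 4, and 6 participants". It names no stratification factor.
- **Analysis.** Statistical analysis says that comparisons of continuous outcomes "will be performed using linear models (General Linear Models-ANCOVA) adjusted for baseline values". It names no other covariate.
- **Description of the sample.** Sample characterization lists comorbidity, cognition, mood, nutrition, medication and other items. Time since fracture is not among them.
- **Recovery after 6 months.** The Background says "few studies have explored the late period of recovery (over 6 months" and adds that limitations can persist in that period. It gives no figure for how recovery differs between, say, 6 and 24 months after fracture.

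**The concern.** Time since fracture defines the study population, so it is recorded before randomisation at no extra effort. With 12 months of follow-up, a participant entering at 6 months is observed from month 6 to month 18, and one entering at 24 months from month 24 to month 36. Baseline SPPB measures current level, not direction of travel. If people nearer their fracture are still improving, two participants with the same baseline SPPB would have different expected follow-up scores whatever their arm.

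A prognostic variable left out of the model stays in the residual variance. The trial is small and sized for just 80% power, so a free reduction in residual variance is worth having. Prespecification matters too: adding the covariate only after the arms are seen to differ would be open to challenge.

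**Working it through.** **1. The plan's own figure.** Inputs from Sample size calculation: difference 1.0 SPPB point, SD 1.48, power 80%, significance level 5% (taken as two-sided), loss 15%.

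n per group = 2 × 1.48² × (1.960 + 0.842)² / 1.0² = 34.4, rounded up to 35.

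Allowing for loss: 34.4 / 0.85 = 40.5, giving 41; starting from the rounded 35, 35 / 0.85 = 41.2, giving 42. The article has "The sample size of this study (41 participants per group"), so its figure reproduces to within one participant. About 35 per group complete.

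**2. How far the arms could differ by chance.** Assumption: entry is uniform over the window.

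- 6 to 24 months: SD = 18/√12 = 5.2 months. SE of the difference in means with 41 per group = 5.2 × √(2/41) = 1.15 months; 95% range about ±2.2 months.
- 6 to 48 months: SD = 42/√12 = 12.1 months. SE = 12.1 × √(2/41) = 2.7 months; 95% range about ±5.2 months.

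**3. What adjustment would gain.** Let R² be the share of SPPB variance that time since fracture explains once baseline SPPB is in the model. The article does not give it, so a range is assumed. The SD of 1.48 is taken as the spread before time since fracture is added. With 35 completers per group:

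- residual SD = 1.48 × √(1 − R²)
- power = Φ(1.0 / [residual SD × √(2/35)] − 1.96)
- narrowing of the confidence interval = 1 − √(1 − R²)
- shift in the unadjusted estimate from an imbalance at its 95% limit = √R² × 1.96 × 1.48 × √(2/35) = √R² × 0.69

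| Assumed R² | Residual SD | Power with adjustment | Interval narrower by | Shift at the 95% limit (points) |
|---|---|---|---|---|
| 0 | 1.48 | 80.7% | 0% | 0 |
| 0.05 | 1.44 | 82.6% | 2.5% | 0.16 |
| 0.10 | 1.40 | 84.6% | 5.1% | 0.22 |
| 0.20 | 1.32 | 88.5% | 10.6% | 0.31 |

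Without adjustment the SD stays at 1.48 and power at 80.7% by this formula (79.6% with the t distribution).

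The last column is not an extra error. The 95% half-width of the unadjusted estimate is 1.96 × 1.48 × √(2/35) = 0.69 points, and the shift is one component of it.

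**4. Check for bias and type I error.** Simulation: 70 completers, blocks of 2, 4 and 6, time uniform over 6 to 24 months, baseline score always in the model, R² of 0, 0.05, 0.10 and 0.20, 4,000 runs per setting.

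- Without time since fracture: mean estimates −0.015 to 0.005 under no effect and 0.997 to 1.009 under a true effect of 1.0; rejection under no effect 5.0 to 5.5%; power 78 to 79%.
- With it: power 78, 80, 83 and 86% for the four R² values; rejection under no effect 4.8 to 5.9%. With normal errors these tests are exact, so departures from 5% are simulation noise.

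**The case against.** A reader might infer that natural recovery is mixed into the exercise effect, or that chance imbalance makes the result invalid. The article does not support either. Allocation is randomised and concealed, and the Control group section provides concurrent usual care, so recovery occurs in both arms and cancels on average. Chance imbalance is already inside the standard error, and step 4 finds neither bias nor an inflated type I error.

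Three further objections stand.

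- **The premise is unproved here.** The article treats the time beyond 6 months as one late stage and nowhere compares recovery early and late in the window. Baseline SPPB also absorbs whatever part of time since fracture acts through current function. The R² values above are therefore assumptions, and zero is among them.
- **There is no shortfall.** If 1.48 is the right SD, the stated size delivers the stated 80% power without the covariate. Adjustment only improves on that.
- **The article is condensed.** Further covariates may sit in an analysis plan that is not shown, and permuted blocks with "linear models (General Linear Models-ANCOVA) adjusted for baseline values" are a sound basic choice for 82 participants. It is also not shown that time since fracture matters more than, for example, age or walking-aid use.

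These points lower the weight of the matter but do not remove it. The variable is in hand, defines the population, and costs almost nothing to use. The conflict between the two windows is on the page whatever one thinks about covariates.

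**Conclusion.** This is a modest efficiency improvement, not a validity error. Time since fracture is named neither in the randomisation nor in the ANCOVA. Prespecifying it would add between nothing and about 8 percentage points of power, as R² runs from 0 to an assumed 0.20. The size rests on three assumptions: the R² range, 35 completers per group, and 1.48 as the SD before time since fracture enters the model.

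One part needs no assumption. The abstract and Participants give an upper limit of 24 months and the Background aim gives 48, and both cannot describe the trial. Under the wider window time since fracture would vary more, and the case for using it could be stronger.

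**What to change.** 1. Prespecify time since fracture, in months at randomisation, as a covariate beside baseline SPPB in the primary ANCOVA. If an analysis plan already does so, the sponsor need only confirm it.
2. Report time since fracture by arm in the baseline table.
3. Reconcile the 6 to 24 month and 6 to 48 month windows across the abstract, Background and Participants.
4. Optionally, stratify the blocks by time since fracture, but only if randomisation has not begun and after the window is reconciled, because the strata depend on it. This means one envelope series per stratum.

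Items 1 and 2 need no new data, visits or participants. The cost is one degree of freedom, with no return if time since fracture is not prognostic given baseline SPPB.

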### Interventions

#### Intervention group

Intervention Group (IG) will undergo a physical exercise program involving progressive and challenging balance training and neuromuscular and functional training of the lower limbs, conducted at home by physiotherapists, once a week, lasting about one hour, in the first, second and third month after randomization and will be taught to perform exercises at home, twice a week, using a booklet.

Visits to monitor and progress the home exercise program will be conducted once a month, from the fourth to the sixth month and each 2 months until the end of the follow up at the 12^th^ month, i.e., a total of 18 sessions. Participants will receive monthly phone calls to encourage exercise adherence. The physical exercise program will consist of balance training and neuromuscular training of lower limbs, as described below:
*Progressive strengthening of three muscle groups: ankle dorsiflexors, knee extensors and hip abductors.* The intensity will be defined individually and will correspond to the adequate amount of weight that would allow them to perform for 10–15 reps, 2–3 sets. Participants will receive ankle cuff weights to perform the exercises.
*Progressive balance training*, consisting of a protocol of exercises with 1 or 2 sets of 10 repetitions, according to individual capacity, to ensure that participants reach their maximum level of functionality [19]. Weight-bearing exercises [14, 15], training with emphasis on perception of the limits of stability, change of position/direction, maintenance of static and dynamic stability, anticipatory adjustments using different bases of support and different sensory conditions will be made. Exercises will include 360° turns, sitting and standing, walking up and down stairs, functional reach, steps in different directions and walk training.

In the first session the physiotherapist will choose two exercises that best address the participant’s functional goals and will add more exercises each week according to the participant’s ability, rate of improvement and motivation. The degree of balance challenge will be progressed in terms of reducing the base of support, the use of hands and the inclusion of multisegmental coordination exercises. Participants will be receive recommendations on how to perform the exercises safely, such as standing near of a table or in the corner of a room, so they can promptly use hands for protection if they start to fall. Those who are frailer will be encouraged to perform exercises under supervision of a caregiver. Participants will receive a detailed booklet, containing photos and instructions for the exercises.

Adverse effects related to the intervention that interfere in the activities of everyday life for more than 48h or require medical attention will be recorded and monitored (pain, discomfort, swelling, etc.). During home-visits the physiotherapist will check how the participant is performing the exercises and progress the exercises if necessary. Participants will receive monthly phone calls to encourage exercise adherence and to collect information about falls and their consequences. Participants will be asked reasons for non-adherence to exercises.

Participants will receive a diary logbook to record the number of falls a week and a guidance booklet containing information about prevention of falls (involving person, environmental and occupational factors), prevention of fractures and bone health. This group will also receive usual health care.

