#### Control group

This group will receive usual care; so will not be disadvantaged by participating in the study. Usual care will be what the participant receives as part of the network of health care which he/she is part of. The participants will receive a diary falls logbook and a guidance booklet containing information about prevention of falls, fractures and bone health. Control group participants will receive monthly phone calls requesting information about falls and their consequences.

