*Physical activity level* will be measured by the self-reported Incidental and Planned Exercise Questionnaire - IPEQ_W [26], ten questions designed to measure physical activity planned and unplanned for older people. The version estimates the intensity of physical activity during the last week will be used. The participant will be questioned for the frequency (every day, 3–6 times per week, twice a week, once a week or less than once per week) and duration of activity (less than 15min per day, more than 15min and under 30min per day, more than 30min and less than 1h, less over 1h and 2h per day more and less than 4h per day 2h, 4h, and daily or more). The total score is derived by multiplying the frequency categories by categories of activity duration, expressed in hours per week.

*Occurrence of falls* will be assessed by monthly phone calls to participants who will be encouraged to use to diary to record the number of falls each day. A structured questionnaire will be used to identify possible falls and their consequences. The intervention group will be compared to control group at 6 and 12 months follow-up in relation to the number of falls (primary outcome) and the proportion of fallers.

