#### Sample characterization

*Functional Comorbidity Index* [27] is an 18-item scale designed to assess comorbidities related to physical function rather than mortality. Each scale item receives 1 point if the patient reports the disease.

*Cognitive function* will be assessed through the Montreal Cognitive Assessment Test (MoCA Test) [28], a battery of tests to detect mild cognitive impairment. The test takes 10min and the maximum score is 30 points. The test assesses different cognitive domains: attention and concentration, memory, language, visuoconstructional skills, conceptual thinking, calculations and orientation.

*Depressive symptoms* assessed by the Geriatric Depression Scale (GDS) [29], an instrument designed to detect depression in the older people. The short version contains 15 items and is the most used in clinical settings due to its rapid application. Each answer has a score of 0 or 1, and a final score above 6 points is considered to be indicative of depression.

*Fall-related self-efficacy*, assessed by the Falls Efficacy Scale International (FES-I) [30] a scale of self-efficacy of fall avoidance during activities of everyday life, which has 16 items with scores ranging from 1 to 4 (maximum total score 64) and a cutoff score of 31 points.

*Nutritional status*, assessed by the Mini Nutritional Assessment (MNA) [31] a questionnaire consisting of two parts: Screening and Overall Assessment. The screening consists of 6 basic questions about weight loss, BMI, mobility and neuropsychological problems. The score in the first part of the assessment can vary from 0 to 14 points. If the score is less than 12, the researcher must continue through the second part of the questionnaire, composed of more specific questions on nutrition and physical assessment. The sum of 18 questions can provide a maximum score of 30. The person with a score greater than or equal to 24 points is considered well-nourished, a score of 17–23.5 is considered at risk for malnutrition, and a score of less than 17 classifies the person as malnourished.

*Number of regular medications*, prescribed by a doctor, in the last 3 months will be computed, except vitamins and other medications for sporadic use (analgesics, for example). The use of psychotropic medications will be specifically recorded.

*Hospitalization and care in emergency department*: duration and reason for hospitalization and duration of stay in the emergency department during the study period.

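### The adverse-effect rule is written only for the exercise arm and only for intervention-related events, so non-fall harms are not ascertained comparably between arms

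*Protocol article*

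**What the plan says.** Under Interventions, Intervention group, the Protocol article says that it will record and monitor "Adverse effects related to the intervention that interfere in the activities of everyday life for more than 48h or require medical attention", with pain, discomfort and swelling as examples. An event must therefore pass two conditions: relatedness to the intervention, and a severity threshold.

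The same section describes the exercise arm's calls: "Participants will receive monthly phone calls to encourage exercise adherence and to collect information about falls and their consequences". It also describes physiotherapist contact, 18 sessions in all: "During home-visits the physiotherapist will check how the participant is performing the exercises and progress the exercises if necessary".

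The Control group section has no adverse-effect rule. It describes the calls in that arm as follows: "Control group participants will receive monthly phone calls requesting information about falls and their consequences".

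Three other places bear on harm:

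- The abstract's Methods paragraph says, without limit to an arm, "Adverse effects will be monitored".
- Secondary outcomes gives a falls instrument not confined to one arm ("A structured questionnaire will be used to identify possible falls and their consequences") and a comparison: "The intervention group will be compared to control group at 6 and 12 months follow-up in relation to the number of falls". Statistical analysis names negative binomial regression for the fall rate.
- Sample characterization lists hospital and emergency care: "duration and reason for hospitalization and duration of stay in the emergency department during the study period". No comparison by arm is stated for it.

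**The concern.** People aged 60 or over who are 6 months to 2 years past a surgically treated hip fracture may well have pain or swelling without any exercise programme. A count of such complaints in the exercise arm can be interpreted only against a count obtained in the same way under usual care. The rule as written does not provide one, because a person who receives no intervention cannot have an effect related to it, and the control calls are not described as asking about anything but falls.

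The relatedness condition can distort the count in either direction. Background pain may be blamed on the exercises, or pain caused by the exercises may be put down to the old fracture and never recorded. The exercise arm also has 18 physiotherapist contacts at which complaints can surface, and none are described for controls.

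At stake is the tolerability half of the trial's message. The Discussion foresees adoption of the programme in the public health system if it proves effective. The problem lies in data collection, so a later analysis plan cannot repair it: symptoms that controls were never asked about cannot be recovered.

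**Working it through.** **Step 1. Set the arms side by side, as the article describes them.**

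| Type of harm | Exercise arm | Usual-care arm | Comparison stated |
|---|---|---|---|
| Falls and consequences | Monthly call, diary | Monthly call, diary | Yes: number of falls and proportion of fallers, at 6 and 12 months |
| Hospital and emergency care | Recorded, no arm restriction | Recorded, no arm restriction | None stated |
| Non-fall effects (pain, discomfort, swelling) | Recorded if related to the intervention and above the threshold | No rule given; call content limited to falls and their consequences | None stated |
| Physiotherapist contacts | 18 sessions | None described | Not applicable |

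Only the third row lacks comparable collection. The second row has the data but no stated use by arm.

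**Step 2. The plan's own figure.** The article gives no adverse-effect rate, so there is no harm figure to reproduce. The only input needed is the group size of 41 from Sample size calculation. It reproduces closely from a difference of 1.0, SD 1.48, 80% power and two-sided 5%: n = 2 × (1.96 + 0.84)² × 1.48² / 1.0² = 34.3, rounded up to 35 per arm. Allowing 15% loss gives 35 × 1.15 = 40.25, rounded up to 41, or 35 / 0.85 = 41.2, rounded up to 42. The point does not depend on this figure.

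**Step 3. Illustration, assumed throughout.** Suppose qualifying complaints are equally common in both arms, but the control count is recorded as 0 of 41 because of the rule. With k exercise-arm participants recorded, the two-sided Fisher p is 2 × C(41,k) / C(82,k):

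- k = 5: 2 × 749,398 / 27,285,336 = 0.055
- k = 6: 2 × 4,496,388 / 350,161,812 = 0.026

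Six is therefore the smallest count that gives p below 0.05 against zero.

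**Step 4. How likely is a count of 6 or more?** Let r be the share of exercise-arm participants recorded with such an effect, that is, true frequency multiplied by the fraction called related. The count is then Binomial(41, r).

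| Assumed r | Expected count, 41 × r | Chance of 6 or more |
|---|---|---|
| 5% | 2.05 | 2% |
| 10% | 4.1 | 22% |
| 15% | 6.15 | 59% |
| 20% | 8.2 | 86% |

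For example, a true frequency of 30% in each arm with half called related gives r = 0.30 × 0.5 = 15%. The answer runs from negligible to likely across a plausible range, and nothing in the article fixes where in that range the trial would fall.

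**The case against.** The strongest reply is that the article covers more than the adverse-effect sentence suggests. In a balance-challenging programme after a fall-related fracture, falls are an obvious potential harm, and they are collected in both arms and formally compared. Hospital and emergency care have no arm restriction, and Statistical analysis says that dichotomous variables will be compared by logistic regression without listing them, so those data may be compared after all. This stands. A reader might infer that harm cannot be compared with usual care at all, and the document does not support that.

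Second, recording only in the exercise arm is inferred from where the rule is placed and from the absence of a counterpart in the Control group section. No sentence says that control events go unrecorded, the abstract's statement is unrestricted, all participants are assessed at home at 3, 6 and 12 months, and a journal article condenses a fuller protocol. This stands in part: control-arm collection may exist elsewhere. But the article does describe what the control calls ask, and the relatedness condition is explicit text. That condition would defeat comparison even if controls were asked under the same rule.

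Third, a reader might infer that unblinded staff decide relatedness. The article names no judge. It says only that assessors are blinded and that participants and therapists are not.

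Fourth, no between-arm test of adverse effects is announced, and the rule can be read as tolerability monitoring of the programme. This is correct. The p-values above describe what the recorded counts could suggest, not an analysis that the article plans. They also use all 41 per arm. With 15% loss, 41 × 0.85 is about 35 per arm, and 6 against 0 gives 2 × C(35,6) / C(70,6) = 2 × 1,623,160 / 131,115,985 = 0.025. The threshold count stays at 6, but it is reached less often at a given rate.

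**Conclusion.** The point holds for non-fall adverse effects. As the article is written, they are recorded under a rule that only exercise-arm participants can satisfy, and no parallel question is described for controls. An exercise-arm count of pain, discomfort or swelling would have no fair comparator.

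It does not extend to falls, which are collected and compared in both arms. For hospital and emergency care the shortcoming is smaller: these events arise after randomisation and are recorded without arm restriction, but they are filed as sample characteristics with no stated comparison.

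The numerical size is unknown. An apparent difference from equal true rates ranges from very unlikely (2% at a recorded rate of 5%) to likely (86% at 20%), assuming that the control count is recorded as zero and that someone compares the two counts. The conclusion does not need these figures, because it follows from the wording of the rule. It assumes that the full protocol adds no control-arm collection. This is a worthwhile and inexpensive improvement. It is not a flaw in the primary comparison.

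**What to change.** In the monthly calls already made to both arms, ask one identical question: has there been any new or worse symptom that meets the protocol's existing threshold (daily activities affected for more than 48 hours, or medical attention required), whatever the cause? Record relatedness as an additional item, not as a condition for counting the event. Report by arm the number of participants with at least one such event, keep events noticed only at physiotherapist visits in a separate column, and report hospital and emergency care by arm as safety data.

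The cost is a slightly longer call and one more table. Self-report would remain unblinded, so some reporting difference could persist even with the same question. If the full protocol already collects these events alike in both arms, one clarifying sentence in the Control group section is enough.
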